### Statistical analysis

The analysis is performed on an intention-to-treat basis. All the patients who have signed the informed consent and attended the initial interview are included. Missing data from the BDI-II evaluation during follow-up will be substituted by the last registered value (Last Observation Carried Forward strategy). At the beginning of the study descriptive statistics will be performed to evaluate the homogeneity between the two groups (IG and CG) with respect to demographic, clinical, and service utilization variables. In order to measure the main objective (rate of remission and response) logistic regression is employed in which the dependent variable is dichotomous (rate of remission and response). The patient’s group is the independent variable. Raw and adjusted odds ratio (OR) are calculated according to age, sex, pharmacologic treatment, and comorbidity. Repeated measure ANOVA analysis will be performed to determine the evolution of the dependent variables during follow-up. For the secondary resulting variables, control of the physical pathologies will be measured by logistic regression in which the dependent variable is dichotomous (control yes/no). The models will be adjusted in the same way as the principal one. Variable differences in the BDI-II rating and other scores with respect to baseline will be calculated. Student’s t test will be employed for the comparison between the groups’ variables and standardized effect size (SES; Kazis et al.1989) [44].

The economic analysis will be carried out with a cost-effectiveness analysis to compare the expenses incurred from the psychoeducation intervention with those from habitual clinical practice over 1 year. The QALYs (quality-adjusted life years) obtained from the EuroQol questionnaire will provide the variable of effectiveness. That of cost will be obtained by measuring all the direct expenses generated by the participants from both groups and including any other related information. For instance, primary care consultations, referrals to specialists, hospitalization, additional tests, analytical tests, and medication expenses. The ratios and incremental costs for the IG versus CG will be calculated. Prices will be based on those of 2016 as the Oblikue database is the most complete for that period. As the healthcare costs will be generated over various years a constant discount rate of 3% per year will be applied. Finally, for the items with the greatest presence in the overall cost, a deterministic sensitivity analysis will be carried out to ensure robustness and reliability of the results obtained [45].

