### Sample

The participants are patients aged > 50 years assigned to PHC from different locations: Barcelona city (1,200,066), the central area of Catalonia (192,000), and the southern area (132,000). Such a territorial representation provides patients from urban, semi-urban, and rural areas.

Inclusion criteria are: 1) the presence of at least one of the following physical diseases: diabetes mellitus type 2, COPD, asthma, and ischemic cardiopathy; 2) a score > 12 on the Beck Depression Inventory score (BDI-II) [21, 22] Spanish version adapted by Sanz et al. [23–25], and confirmation of major depression according to DSM-IV criteria with the Mini International Neuropsychiatric Interview (MINI); 3) adherence to a one-year follow-up with the same PHC team; 4) signed informed consent.

Exclusion criteria are: 1) diagnosis of dementia or moderate/elevated cognitive decline (5 or more errors on the Pfeiffer scale); 2) major depressive disorder with psychotic symptoms or other serious psychiatric comorbidities; 3) elevated/moderate risk of suicide (a score of ≥6 on the MINI scale); 4) drug of abuse dependence disorders (including alcohol); 5) physical illness at an advanced stage; 6) inability to attend the PHC; 7) under psychological therapy from the Community Mental Health Team; 8) inability to understand Spanish/Catalan.

Patients receiving anti-depressive/anxiolytic treatment are not excluded. Their data are collected and considered as covariables.

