### Sample size

A power analysis will be conducted to determine the appropriate sample size. A previous study of psychoeducation programs [18] reported a remission rate at 9 months follow-up of 40% in the IG and 26% in the CG. Assuming a 5 and 20% alpha and beta risk, respectively, 189 patients are required for each group. Due to a number of reasons, an approximately 25% dropout rate is expected, consequently, 252 participants per group need to be recruited (total *n* = 504). In addition, 25 PHC are required each with a mean of 20 patients (IG *n* = 10, CG *n* = 10).

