### Recruitment process

The recruitment process for the trial began in September 2017. All eligible PHC located in Barcelona city, the central area of Catalonia (Bagés, Berguedá, and Solsonés) and the southern area (Baix Llobregat Nord) have been contacted and encouraged to participate in the study. The PHC who express interest receive a team presentation, explanatory dossiers, and informed consent papers. Those who wish to take part are required to consecutively recruit 16–24 patients who, after meeting inclusion criteria and signing the informed consent, will be randomized into two equally sized groups (IG and CG).

Different groups of healthcare workers will be involved in the field work:Recruiters: the patient’s assigned doctor and/or nurse.Nurses leading the psycho-educational groups, two per PHC.Evaluators blinded to the groups who carry out interviews at baseline, and at 3 months, and 12 months post-intervention.An external researcher in charge of patient randomization which is performed once all the necessary number of patients have signed the consent forms. The data gathering phases are explained in the work plan section.

All outcome variables will be assessed three times: prior to study commencement (baseline), after 3 months, and at 12 months after inclusion in the individual data collection sessions. Information about data collection and intervention programme timeline are detailed in the Table 2.

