Sex, age, civil status, educational level (without studies / incomplete primary ones / completed primary ones / secondary ones / higher education), employment status (employed / housewife / unemployed / disabled / retired). Assigned PHC: rural (doctor’s surgery) / semi-urban (PHC with a population < 15,000 inhabitants) / urban (PHC with a population ≥ 15,000 inhabitants).

Primary outcomes*Clinical remission and/or response of depression* at short and long-term (one year follow-up) of the intervention following Riedel et al. [32]: clinical remission considered as a reduction in the rating < 13 of the BDI-II; response to the intervention as a decrease of at least 50% in the initial evaluation of depressive symptoms according to the BDI-II.

Secondary outcomes

*Improvement in the control of the chronic pathology* at 12 months follow-up:
Diabetes mellitus: controlled with glycosylated hemoglobin, HBA1C (%) [33, 34].COPD: lung function measured by post bronchodilator expiratory volume (FEV1). Dyspnea evaluated by the modified score of the Medical Research Council (mMRC), at 5 points [35, 36]Asthma: lung function measured by post bronchodilator expiratory volume (FEV1). Determination of peak expiratory flow (PEF) [37].Ischemic cardiopathy: measurement of levels of low-density lipoprotein cholesterol and blood pressure [38].
2.*Adherence to medication* is assessed by the *Morinsky-Green* test [39] and the comparison between containers collected in the pharmacy and those prescribed. It will be performed for all the prescribed medication for both groups.3.*Quality of life* as measured with the *EuroQol (EQ-5D-5 L)* questionnaire. (Original: EuroQol Group 1996. Spanish adaptation: Badia et al. 1999) [40, 41].4.*Utilization of healthcare services* during the study period. This includes: number of hospital admissions (emergency room and ward) due to complications arising from diabetes, COPD, and ischemic cardiopathy (yes/no), and psychiatric pathology (yes/no); mental health referrals (yes/no) and number; and consultations with the family doctor/nurse (yes/no) and number.5.*Variables resulting from the intervention with respect to its feasibility.* A questionnaire with 10 items and a Likert scale of 4 categories regarding satisfaction is administered to the patients on completing the intervention. Adherence is assessed through the number of sessions each IG patient attends. An adherence variable is calculated for the intervention: ≥75% attendance or less.

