Some limitations include the fact that the nurses who carry out the intervention are aware of the groups the patients belong to. Nevertheless, blinding of some key stages of the study, such as randomization, evaluation of outcomes/confounder variables, and statistical analysis will be maintained. Second, for a long-term follow-up under normal conditions a dropout rate of 25% is expected. In the case of missed appointments and intervention sessions it is hoped that patient adherence will be ensured through telephone calls (at least three times per appointment, one of which is 24 h prior to the appointment) unless the patient has stated reluctance to participate. Third, the patients will present varying pathologies which will increase the heterogeneity of the sample. Nevertheless, most of the patients attended at the PHC present comorbidities and their inclusion represents a greater generalization of results. Fourth, in order to avoid the effect of contamination, patients assigned to the two nurses leading the IG from the same center will be excluded. Fifth, there could be some difficulty in recruiting a sufficient number of patients.

To the best of our knowledge, this is the first study evaluating the effectiveness of a psychoeducation group intervention with patients suffering from both depression and a chronic organic pathology (diabetes mellitus, COPD, asthma, and ischemic cardiopathy) to be carried out by community nurses in a primary care setting.

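### Under LOCF every patient lost before the 3-month visit counts as a failure by construction, so unequal early loss between the arms would bias the primary odds ratio in either direction

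*Protocol article*

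**What the plan says.** Four statements in the protocol article combine here.

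- **Entry (Sample):** "a score > 12 on the Beck Depression Inventory score (BDI-II"), with major depression confirmed by interview. The Abstract gives the entry range as 13–28.
- **Primary outcome (Measures):** "clinical remission considered as a reduction in the rating < 13 of the BDI-II". Response is a fall of at least 50% from the initial score. Both short-term and one-year status belong to the primary outcome.
- **Missing data (Statistical analysis):** "Missing data from the BDI-II evaluation during follow-up will be substituted by the last registered value (Last Observation Carried Forward strategy"). The analysis set is everyone who consented and attended the initial interview, so dropouts stay in the denominator. The comparison is a logistic regression reported as an odds ratio. A repeated-measures ANOVA and t tests on changes from baseline follow.
- **Sample size:** the source study "reported a remission rate at 9 months follow-up of 40% in the IG and 26% in the CG". From these two rates the article derives 189 per arm at 5% alpha and 80% power. It then allows for loss: "an approximately 25% dropout rate is expected, consequently, 252 participants per group need to be recruited".

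The Discussion ties the dropout figure to the whole follow-up: "for a long-term follow-up under normal conditions a dropout rate of 25% is expected". The article does not split it by arm or by time.

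**The concern.** The rule does not leave the status of an early dropout open. The carried-forward baseline score is at least 13, so it can never be below 13. Its change is 0%, so it can never be a 50% fall. Losing a patient before the first follow-up has the same effect on the primary outcome as observing a failure. A patient lost after the 3-month visit keeps the 3-month status at 12 months, whatever happened in between.

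A difference in early retention is thereby converted into a difference in remission. Such a difference is plausible: one arm is asked to attend 12 weekly sessions of 90 minutes, and the other continues usual care. The direction cannot be predicted, so the rule cannot be defended as conservative. The filled-in scores also enter the ANOVA and the t tests as if they had been observed.

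A second, lesser issue is that the Sample size section takes dropouts out of the analysed number, whereas the analysis keeps them.

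**Working it through.** **1. The plan's own figure.** Inputs from Sample size: 40% v 26%, alpha 5%, power 80%. From Recruitment process: 1:1 allocation ("will be randomized into two equally sized groups (IG and CG")). The two-sided normal-approximation formula with mean rate 0.33 gives 176 per arm:

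n = [1.96·√(2·0.33·0.67) + 0.842·√(0.40·0.60 + 0.26·0.74)]² / 0.14² = 175.9

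With the continuity correction it gives 190, which matches the stated 189 to within one patient. Then 189 / 0.75 = 252. Power at 189 per arm is 79.8% with the correction.

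**2. Effect of LOCF on the observed rate.** Let e be the share of an arm lost before 3 months. If those patients would have remitted at the same rate p as the others:

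observed rate = p × (1 − e)

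For patients lost after 3 months I assume that the carried-forward status has the same rate p.

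**3. Unequal early loss.** The loss rates are assumptions, since the documents give none by arm. There are 252 per arm. The rejection rate comes from the two-sided 5% test of two proportions, without continuity correction. IG is the intervention group and CG the control group.

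| True remission IG / CG | Early loss IG / CG | Observed IG / CG | Difference | Rejection rate |
|---|---|---|---|---|
| 30% / 30% | 20% / 30% | 24.0% / 21.0% | 3.0 points, spurious | 12.7% |
| 30% / 30% | 10% / 15% | 27.0% / 25.5% | 1.5 points, spurious | 6.7% |
| 40% / 26% | 30% / 20% | 28.0% / 20.8% | 7.2 points | 47% |
| 40% / 26% | 20% / 30% | 32.0% / 18.2% | 13.8 points | 95% |

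For the first row, the standard error is √(2·0.225·0.775/252) = 0.0372, so a spurious 0.03 shifts the test statistic by about 0.8.

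**4. Equal early loss.** With no true effect both observed rates are p(1 − e), so the difference is zero and the type I error stays at 5%. With the planned effect the difference is 0.14 × (1 − e). Power at 252 per arm, with the continuity correction that comes closest to the stated 189 (n replaced by n − 2/d + 1/(n·d²), where d is the difference), is:

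| Early loss, both arms | Rates | Difference | Power |
|---|---|---|---|
| 0% | 40.0% / 26.0% | 14.0 points | 90% |
| 12.5% | 35.0% / 22.75% | 12.25 points | 84% |
| 18% | 32.8% / 21.3% | 11.5 points | 80% |
| 25% | 30.0% / 19.5% | 10.5 points | 75% |

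Without the correction the last row is 78%. Power stays near plan because LOCF analyses all 252 per arm, where the Sample size section counted on 189. These figures ignore any clustering by centre or therapy group.

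**The case against.** The strongest reply is that the harm depends on something the documents do not show. With equal early loss the test keeps its size and the treatment effect still decides the result. The plan gives one overall dropout figure, describes at least three telephone calls per appointment to protect retention, and cites attendance of 73–87% in comparable programmes. A small difference in loss does little: 10% against 15% raises the rejection rate only to 6.7%. All of this stands. A reader might infer that dropout itself drives the primary result; the documents do not support that, because it needs a difference between arms that they neither report nor predict.

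A reader might also infer that the trial is planned for 14 points but will see only 10.5. That figure is a bound. It puts the whole 25% before the 3-month visit, although the Discussion attaches it to long-term follow-up. It also takes 40% and 26% as completer rates, which the article does not say; if the source study already counted dropouts as failures, there is no further dilution. Power falls below 80% only when equal early loss exceeds about 18%.

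Finally, counting missing as non-remission is a recognised choice for a binary remission endpoint, and imputation details and sensitivity analyses normally belong in the SAP, which is not shown. Their absence is not criticised here. The article, however, does fix the primary rule, and that rule is not a consistent missing-equals-failure definition: early losses are failures, while late losses keep whatever status they had at 3 months. The exposure to unequal early loss remains.

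**Conclusion.** The point holds as a defect in a stated rule. Entry threshold, outcome definition and LOCF together make every patient without a follow-up score a certain failure on both components of the primary outcome, and freeze later losses at their 3-month status. The primary odds ratio is biased whenever early loss differs by arm, in whichever direction the difference runs.

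The size is unknown from the documents. Under the assumed loss rates above, the false-positive rate is 6.7% to 12.7%, and power for the planned effect ranges from 47% to 95%. These figures rest on assumed losses by arm, on all of that loss falling before 3 months, and on dropouts having the same true remission rate as the others.

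The Sample size and Statistical analysis sections do use different bases for dropouts, and they should be aligned. The net effect on power is small: 90% down to 75% across the whole range of equal early loss, against a planned 80%. The case for change therefore rests on the risk of unequal loss, not on lost power.

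**What to change.** - **Primary analysis:** multiply impute the BDI-II score within arm, derive remission and response from the imputed score, and keep the planned logistic regression. Alternatively, fit a likelihood-based mixed logistic model to the observed 3- and 12-month outcomes; its odds ratio is conditional on the patient, so the text should say so.
- **Course over time:** replace the repeated-measures ANOVA on filled-in values with a linear mixed model on observed BDI-II scores.
- **Sensitivity:** keep LOCF, or missing counted as non-remission, as a sensitivity analysis only.
- **Sample size:** state it on the same handling of dropouts as the primary analysis, and say whether 40% and 26% are rates among completers or among all randomised patients.

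The cost is revised wording and some programming, with no new data. The replacement relies on data being missing at random, which cannot be verified; a sensitivity analysis that departs from that assumption can show how far the conclusion depends on it.

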## Background

Depression is considered a major public health issue in industrialized societies [1], and has been associated with greater morbidity and mortality, and increased healthcare utilization and costs [2–4]. In primary care, depression is one of the most frequent causes of consultation [5] and is particularly common in patients with physical illnesses. The prevalence of depression worldwide is 4.4%, in Spain it represents 5.2% [6] reaching up to 30% in populations with chronic physical conditions when taking into account symptoms and disorders [2]. For instance, in diabetic patients the risk of depression is twice that of the general population [2]. According to the World Health Organization (WHO) by 2030 it will be the principal cause of disability in the world [7].

The concomitance of physical illness and depression not only decreases the patient’s response to anti-depressive treatment but also worsens control of their organic pathologies, results in unhealthy habits (diet and exercise), and leads to lower treatment compliance [8]. As a consequence, the economic burden of healthcare is greater in such individuals with depression than those without [7]. For instance, patients with depression and chronic obstructive pulmonary disease (COPD) can present exacerbations of common respiratory symptoms which require a greater number of visits to the emergency room and hospitalization [9]. It is thus becoming increasingly necessary to design strategies aimed at detecting and treating depression in patients with associated physical comorbidity in order to reduce depressive symptoms and disorders, and improve general health.

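### As written, the carry-forward rule scores a patient who remits at 3 months and then dies as a one-year remission; a minor correction to the primary outcome

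*Protocol article*

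**What the plan says.** Three statements in the protocol article combine here.

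- **Missing scores** (Statistical analysis): "Missing data from the BDI-II evaluation during follow-up will be substituted by the last registered value (Last Observation Carried Forward strategy"). No reason for missingness is set apart.
- **Analysis set** (Statistical analysis): intention to treat, and "All the patients who have signed the informed consent and attended the initial interview are included". Nobody leaves the denominator because of death.
- **Primary outcome** (Measures): remission and/or response, taken "at short and long-term (one year follow-up) of the intervention". Remission is "clinical remission considered as a reduction in the rating < 13 of the BDI-II". Response is "response to the intervention as a decrease of at least 50% in the initial evaluation of depressive symptoms according to the BDI-II". Both depend only on the score; neither requires the patient to be alive or assessed at one year.

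The Recruitment process section places the assessments "prior to study commencement (baseline), after 3 months, and at 12 months after inclusion". The Sample section requires a baseline BDI-II above 12. Death is not mentioned as an outcome or as a reason for a missing score.

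**The concern.** A patient who has died has no 12-month depression score to recover, so death is not an ordinary missing measurement. Under the stated rule the 3-month value stands in for it, and an early remitter who dies becomes a long-term success on the primary outcome.

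The rule also treats the same event in opposite ways according to timing. A death before the 3-month visit carries forward a baseline score above 12 and counts as a failure. A death after an early remission counts as a success.

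The direction matters more than the size. If the intervention produces more early remitters, equal mortality still creates more carried remissions in the intervention group, so the error leans towards the trial's hypothesis. Replacing last observation carried forward by multiple imputation or a mixed model would not cure this by itself, since those methods would also assign a score after death. The plan has to say what the outcome is for a patient who has died.

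Deaths within the year are plausible. Patients are over 50 and have diabetes, COPD, asthma or ischemic heart disease, and the Background says that depression "has been associated with greater morbidity and mortality".

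**Working it through.** **Inputs from the protocol.** Remission 40% (intervention) and 26% (control), a difference of 14 points; alpha 5%, power 80%; 189 per group, 252 after 25% dropout, 504 in total (Sample size). Assessments at 3 and 12 months.

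**Assumptions, because the documents give no figure.** One-year mortality 1–3%, spread evenly over time. One third of patients in remission at 3 months, close to the mean of the two planned rates: (40 + 26)/2 = 33%.

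**1. The plan's own figure.** Without continuity correction, the two-sided two-proportion formula is

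n = [1.96·√(2 × 0.33 × 0.67) + 0.842·√(0.40 × 0.60 + 0.26 × 0.74)]² / 0.14² = 175.9, so 176.

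With continuity correction, n/4 × [1 + √(1 + 4/(n × 0.14))]² = 189.9, which is 190 rounded up, against 189 stated. Then 189/0.75 = 252, as stated. The sample size reproduces within rounding and does not depend on this point.

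**2. Which deaths matter.**

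| Time of death | Value carried to 12 months | Scored at 12 months |
|---|---|---|
| Before the 3-month visit | Baseline, above 12, no change | Not remitted, not responded |
| After 3 months, not in remission or response then | 3-month value | Not remitted, not responded |
| After 3 months, in remission or response then | 3-month value | Remitted or responded |

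Only the last row is misclassified. The interval between the two follow-up visits is 9 months, so 9/12 of a year's deaths are at issue.

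**3. How many patients.**

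- Deaths in a year: 504 × 0.01 to 0.03 = 5.0 to 15.1.
- Deaths between 3 and 12 months: × 9/12 = 3.8 to 11.3.
- In remission at 3 months: × 1/3 = 1.3 to 3.8, about 1 to 4 patients.
- Extreme, all in one arm: 3.8/252 = 1.5 points.

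**4. Effect with equal mortality.** Let d be the share dying between 3 and 12 months, and let those who die have remitted at their arm's planned rate. Counting them as failures multiplies each rate by (1 − d), so the difference falls by 14.0 × d.

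| d | Carried remissions, intervention (252 × d × 0.40) | Carried remissions, control (252 × d × 0.26) | Fall in difference, points |
|---|---|---|---|
| 0.75% (1% a year) | 0.8 | 0.5 | 0.105 |
| 1% | 1.0 | 0.7 | 0.14 |
| 2.25% (3% a year) | 2.3 | 1.5 | 0.315 |
| 3% | 3.0 | 2.0 | 0.42 |

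The shift is about 0.1–0.4 points. For d of 1% and 3% the difference becomes 13.9 and 13.6 points.

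The analysis is by logistic regression, so on the odds-ratio scale: (0.40/0.60)/(0.26/0.74) = 1.90. At d = 1%, (0.396/0.604)/(0.2574/0.7426) = 1.89. At d = 3%, (0.388/0.612)/(0.2522/0.7478) = 1.88.

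Power at 252 per arm is 91.9% with no deaths, 91.5% at d = 1% and 90.7% at d = 3%.

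**5. Unequal mortality.** If 2% die between 3 and 12 months in the intervention group only, its rate becomes 0.40 × 0.98 = 39.2% and the difference 13.2 points. At 5% it is 38.0% and 12.0 points; that is beyond the assumed range and marks a far bound only.

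**The case against.** The strongest reply is that the protocol never mentions death. Including deaths under the carry-forward rule is a reading of unqualified wording in a condensed article, and an analysis plan that is not shown may treat death separately. This limits the certainty, not the point: the article fixes a rule and a denominator, and an exception would have to depart from both.

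The second reply is size. Advanced physical illness, inability to attend the centre and moderate or high suicide risk are all exclusions, which lowers expected deaths. The same carry-forward rule applied to the expected 25% dropout matters far more. This stands, and it is why the point is minor.

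The third reply is that counting death as failure is one choice of estimand and that status while alive is another. That is fair. But the protocol names a one-year outcome and does not define it as status while alive.

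A reader might infer more than the document supports:

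- **That QALYs are overstated in the same way.** The carry-forward rule names only the BDI-II. For the economic analysis the protocol says "The QALYs (quality-adjusted life years) obtained from the EuroQol questionnaire will provide the variable of effectiveness" and states no carry-forward of those values. How death enters the QALY is detail an article may leave to the full plan.
- **That Table 3 is defective because it lists no vital status.** That is an omission from a condensed table.
- **That every death among early remitters' share of one-year mortality counts**, giving 15.1 × 1/3 = 5.0 patients and 5/252 = 2.0 points. This includes deaths before 3 months, which carry a baseline score and already count as failures.

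**Conclusion.** The point holds as a minor correction. Taken together, the missing-score rule, the analysis set and the score-only outcome definition count a patient who remits or responds at 3 months and then dies as a one-year success, and one who dies before 3 months as a failure.

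About 1 to 4 of 504 patients would be affected. The likely bias is a few tenths of a percentage point towards the arm with more early remitters, and 1.5 points is an extreme that needs the highest assumed mortality and every case in one arm. The mortality rate, its even spread and the one-third early remission share are all assumptions. The figures are for remission; the protocol gives no planned response rates from which to size the effect on response. The trial's conclusion is unlikely to turn on this, but the classification is wrong and easily put right.

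**What to change.** In the Statistical analysis section:

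1. Limit carry-forward, or any method that replaces it, to patients who are alive but not assessed.
2. State that a patient who has died by an assessment counts as not remitted and not responded at that assessment, in both arms.
3. Report the number of deaths by arm.

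The cost is two or three sentences. No change to the sample size is needed: power at 252 per arm stays above 90% for equal mortality of 1–3% between 3 and 12 months. The downside is small: deaths unrelated to depression count as failures, so remission rates fall slightly in both arms.
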